# The PLANES study: a protocol for a randomised controlled feasibility study of the placental growth factor (PlGF) blood test-informed care versus standard care alone for women with a small for gestational age fetus at or after 32 + 0 weeks’ gestation

**DOI:** 10.1186/s40814-020-00722-x

**Published:** 2020-11-19

**Keywords:** Fetal growth restriction (FGR), Intrauterine growth restriction, Small for gestational age (SGA), Placenta, Placental growth factor, Soluble fms-like tyrosine kinase

## Abstract

**Background:**

Stillbirth remains a major concern across the globe and in some high-resource countries, such as the UK; efforts to reduce the rate have achieved only modest reductions. One third of stillborn babies are small for gestational age (SGA), and these pregnancies are also at risk of neonatal adverse outcomes and lifelong health problems, especially when delivered preterm. Current UK clinical guidance advocates regular monitoring and early term delivery of the SGA fetus; however, the most appropriate regimen for surveillance of these babies remains unclear and often leads to increased intervention for a large number of these women. This pilot trial will determine the feasibility of a large-scale trial refining the risk of adverse pregnancy outcome in SGA pregnancies using biomarkers of placental function sFlt-1/PlGF, identifying and intervening in only those deemed at highest risk of stillbirth.

**Methods:**

PLANES is a randomised controlled feasibility study of women with an SGA fetus that will be conducted at two tertiary care hospitals in the UK. Once identified on ultrasound, women will be randomised into two groups in a 3:1 ratio in favour of sFlt-1/PlGF ratio led management vs standard care. Women with an SGA fetus and a normal sFlt-1/PlGF ratio will have a repeat ultrasound and sFlt-1/PlGF ratio every 2 weeks with planned birth delayed until 40 weeks. In those women with an SGA fetus and an abnormal sFlt-1/PlGF ratio, we will offer birth from 37 weeks or sooner if there are other concerning features on ultrasound. Women assigned to standard care will have an sFlt-1/PlGF ratio taken, but the results will be concealed from the clinical team, and the woman’s pregnancy will be managed as per the local NHS hospital policy. This integrated mixed method study will also involve a health economic analysis and a perspective work package exploring trial feasibility through interviews and questionnaires with participants, their partners, and clinicians.

**Discussion:**

Our aim is to determine feasibility through the assessment of our ability to recruit and retain participants to the study. Results from this pilot study will inform the design of a future large randomised controlled trial that will be adequately powered for adverse pregnancy outcome. Such a study would provide the evidence needed to guide future management of the SGA fetus.

**Trial registration:**

ISRCTN58254381. Registered on 4 July 2019

## Background

The stillbirth rate within the United Kingdom (UK) remains one of the highest in high-resource countries (3.87 per 1000 births) [1], but stillbirths remain rare at term (2.0 per 1000 births) [2]. Historically strategies to prevent stillbirth have focused on the identification of risk factors in early pregnancy [3–9]. However, risk factors present at booking predict less than 20% of all stillbirths [8]. Furthermore, 33% of stillbirths occur after 36 + 0 weeks, 85% prior to labour with the cause of death unknown in 39% [8]. A third of all stillbirths however are small for gestational age (SGA), and therefore, targeted identification and intervention on the small fetus has become an attractive surrogate strategy to prevent subsequent stillbirth [8]. Even when identified antenatally, SGA fetuses are at a significantly higher risk of stillbirth (odds ratio 7.0, 95% confidence interval 3.3–15.1) [10–12], neonatal adverse outcome [13] and potential life-long health risks [14, 15].

The standard approach advocated by the National Institute for Health and Care Excellence (NICE) for all pregnant women in the UK to identify the SGA fetus relies upon serial measurement of the maternal abdomen with a tape measure from 24 weeks to generate the symphysial fundal height (SFH) [16]. SGA is suspected when the SFH measurement is < 10th centile or there is static growth over two measurements. SFH measurement in isolation has a sensitivity of 30–40% [17, 18] and with no randomised controlled studies of its effectiveness [19]. Therefore, confirmatory ultrasound assessment is required, with SGA commonly defined as an estimated fetal weight (EFW) < 10th centile [4, 17, 20]. However, the increase in detection of SGA with ultrasound is limited, with up to 41% of SGA fetuses remaining undiagnosed and a false positive rate of up to 20% [18].

The Royal College of Obstetricians and Gynaecologists (RCOG) has produced guidance for the management of the SGA fetus [17], but the Cochrane Collaboration acknowledges that the most appropriate regimen for antenatal surveillance is unclear [19]. This guidance advocates that the SGA fetus should have growth assessed with ultrasound every 2 weeks with additional fetal blood flow (Doppler) assessments. Timing of delivery is based upon deterioration in fetal growth or fetoplacental Doppler (< 37 weeks) or when the pregnancy reaches 37 + 0 weeks’ gestation even if all other factors are normal [17]. Therefore, the UK National Health Service (NHS) currently has a system for the management of the SGA fetus and prevention of stillbirth based upon SFH and confirmatory ultrasound with delivery from 37 + 0 weeks. This ‘one size fits all’ approach maintains a safety margin to prevent stillbirth but leads to an increase in interventions, such as induction of labour (IOL) [21]. IOL rates for SGA are increasing (3.0% in 2012 to 10.7% in 2016) with up to 40% of all labours now induced [22].

Our recent survey of UK obstetric units demonstrates that this is a UK-wide phenomenon with mean induction rates at 30% (range 17–46%) [22], with 67% of responders observing an increase over 5 years and 90% stating that in their opinion management of SGA had been a factor. This increased intervention and delivery of SGA fetuses at a late preterm or early term gestation, whilst well intentioned is not without concern. There is a substantial body of evidence showing that being born < 39 weeks has an impact upon a child’s cognitive development and later academic achievement [23–26]. Furthermore, whilst overall numbers of affected children are low, the term SGA fetus has a cerebral palsy risk 5–7 times greater than normal birth weight babies [27, 28]. There is also an impact on women’s choice as to place and mode of birth, especially when in general the risk of stillbirth is low [29] with intervention potentially not required for all SGA fetuses.

### Rationale for study population

The desire to reduce stillbirth is powerful, but due to the relative infrequency of this outcome, it currently leads to increased intervention for a large number of women, which impacts upon a women’s choice and increases the burden on the health care system. However, most importantly whilst small gains have been made in stillbirth reduction in the UK, the goal of significantly reducing stillbirth remains distant. Not all national guidelines are as prescriptive on the management of SGA, recently reviewed by McCowan et al. [30]. Canadian [31] guidance suggests close monitoring of the fetal condition with ultrasound after 37 weeks but with no defined time to deliver. Irish [32], US, and New Zealand guidance [33] is also more flexible suggesting that in the presence of normal Doppler studies the SGA fetus can be left until 38–39 or 40 weeks respectively. Much of this evidence for lack of harm from delaying delivery comes from the DIGITAT study that showed no adverse effects from induction of labour vs delayed delivery [34], though this study was underpowered to offer unequivocal evidence regarding perinatal mortality or severe morbidity. Recently, some reaction against early delivery for SGA in the absence of other risk factors has been observed with a recent UK study deferring delivery until 40 weeks if fetal assessment was normal [35]. However, in this study there was a single stillbirth in the deferred cohort possibly suggesting that additional reassurance of fetal wellbeing is required.

We suggest a potential ‘middle ground’ would be to refine the risk of adverse pregnancy outcome in SGA pregnancies with biomarkers of placental function, namely the sFlt-1/PlGF ratio. We feel that this may help clinicians to differentiate the fetus that is constitutionally small from that which has a reduced growth velocity due to placental failure. Identifying the group at highest risk of stillbirth would reduce the number of interventions performed and reduce the number of babies delivered early whilst maintaining a safety margin to prevent stillbirth. This would represent a more detailed monitoring system than any other nation currently advocates. It would also align with the recent Saving Babies’ Lives Care Bundle, which advocates individualised risk assessments of SGA pregnancies and deferring delivery to 39 weeks in those pregnancies with no high-risk features [36].

### Justification for intervention and biomarkers

The use of biomarkers to identify the fetus at risk of stillbirth has been highlighted as a priority by the RCOG [17] and the James Lind Alliance [37]. However, their low predictive accuracy in the first trimester has limited their use as a screening tool [3]. Recent advances in our understanding of which biomarkers are clinically relevant in late pregnancy has demonstrated that identification of placental disease potentially predisposing to stillbirth is possible [38]. Principal among the biomarkers currently available is placental growth factor (PlGF). This protein is produced by the placenta and identifiable in maternal blood from 12 weeks [39]. Two commercially available platforms which measure PlGF (Alere®) [40] or PlGF relative to sFlt-1 (sFlt-1/PlGF ratio) (Roche®) [41] have been endorsed by NICE for the investigation of hypertension in pregnancy [42]. Whilst the majority of studies have focused on the ability of these tests to predict preeclampsia, there is a significant amount of information on their ability to predict stillbirth and SGA. Abnormally low levels of PlGF in maternal plasma have been linked to preeclampsia [40, 43, 44], SGA [45, 46], and stillbirth [40, 47]. Furthermore, an abnormal PlGF appears to more than double adverse pregnancy outcome [48] and is associated with critical fetal growth restriction [49–53]. In a cohort of SGA fetuses, low PlGF was associated with preterm delivery, stillbirth, birth weight < 3rd centile, Apgar < 7 at 5 min, NICU admission and placental pathology [40, 54, 55]. Women with the lowest PlGF values were in addition much more likely to have a growth-restricted fetus and abnormal Dopplers [40, 47]. In all published studies to date, very few fetuses have been stillborn following a normal PlGF result [40, 47, 53, 56, 57]. The ratio of PlGF to soluble FMS-like tyrosine kinase-1 (sFlt-1), which binds PlGF in the circulation, is increased in preeclampsia [41], fetal growth restriction [58] and stillbirth [59]. An abnormal sFlt-1/PlGF ratio of > 38 is associated with an increased risk of SGA (21% vs 7%) [60]. The sFlt-1/PlGF ratio appears to be equally useful in determining outcome with almost no stillbirths when the ratio is normal [41, 56, 57, 59, 60] (Table 1). A recent Cochrane Diagnostic Test Accuracy Review on the effectiveness of biomarkers to predict stillbirth [61] confirms that abnormal PlGF or sFlt-1/PlGF ratio has a diagnostic odds ratio of 49.2 for subsequent stillbirth. Therefore, PlGF or sFlt-1/PlGF ratio appears to be effective in identifying the fetus that is SGA and more importantly, those fetuses that go on to be stillborn.

**Table 1 Tab1:** Stillbirths by normal and abnormal PlGF and sFlt-1/PlGF ratio

Author	Year	Stillbirth normal PlGF	Stillbirth abnormal PlGF	Stillbirth normal sFlt-1/PlGF ratio	Stillbirth abnormal sFlt-1/PlGF ratio
**Chappell et al.** [40]	**2013**	0	7	-	-
**Benton et al.** [53]	**2016**	1	6	-	-
**Zeisler et al.** [41]	**2016**	-	-	1	3
**Sovio et al.** [59]	**2017**	-	-	0	0
**Sharp et al.** [47]	**2018**	0	1	-	-
**Sharp et al.** [56]	**2018**	0	35	0	35
**Navaratnam et al.** [57]	**2017**	0	1	0	1
**Total**		1	50	1	39

### Objective

The PLANES study (Placental Growth Factor Led Management of the Small for Gestational Age Fetus) has the following overall objectives: (1) to assess the feasibility of delivering sFlt-1/PlGF ratio led management of women with an SGA fetus, (2) to assess the acceptability of such an approach to women and clinicians, and (3) to explore the feasibility/acceptability of the study design.

Results from this feasibility study will inform the design of a future large randomised controlled trial (RCT) powered for adverse pregnancy outcome.

## Methods/design

The PLANES study is a randomised controlled feasibility study of standard care versus sFlt-1/PlGF ratio led management of pregnant women with an ultrasound diagnosis of an SGA fetus (defined as having an EFW < 10th percentile for gestation) at 32 + 0 to 37 + 6 weeks’ gestational age. The 10th centile will be defined by what is considered to be usual practice for each site; both sites in the pilot study use the customised GROW chart. This integrated mixed method study will also involve a health economic analysis and a perspectives work package exploring trial feasibility through interviews and questionnaires with randomised patients and their partners, as well as a clinician focus group and/or questionnaires and interviews.

### Participants

Inclusion criteria are women with a singleton pregnancy, confirmed SGA fetus (EFW < 10th centile on ultrasound within preceding 72 h), normal umbilical artery Doppler (pulsatility index < 95th centile), between 32 + 0 and 37 + 6 weeks of gestation, maternal age > 16 years old and able to give written informed consent. Exclusion criteria are known or suspected structural/chromosomal fetal abnormalities, either absent or reversed end diastolic flow in the umbilical artery on Doppler study, and severe maternal disease requiring urgent delivery. Participation in the perspectives work package follows the same criteria for participants, with the additional exclusion criteria of women who do not speak English. The flow of each participant from consent through to follow-up is shown in Fig. 1.

**Fig. 1 Fig1:**
[figure not shown]
PLANES patient flow diagram

### Intervention

Following randomisation, women will be asked to provide a blood sample for assessment of sFlt-1/PlGF ratio; the result of which will be revealed (biomarker led) or concealed (standard care) from the attending clinical team.

Within the revealed/biomarker led care group, participants with a normal sFlt-1/PlGF ratio (≤ 38) will be advised that their risk of an adverse pregnancy outcome is low and will be offered delivery at 40 + 0 weeks gestation. Women will be offered further ultrasound and sFlt-1/PlGF ratios every 2 weeks, to ensure that they do not become high risk, with the care pathway adjusted if necessary (see Fig. 1). Participants with an abnormal sFlt-1/PlGF ratio (> 38) will be advised to attend for detailed ultrasound assessment by a fetal medicine expert within 72 h of the abnormal result being known. This assessment will involve fetal biometry and Doppler of the umbilical artery (UA), middle cerebral artery (MCA), and ductus venosus (DV). If Doppler studies are normal, then, delivery will be advised from 37 + 0 weeks [17]. If there is evidence of critical fetal compromise (absent end diastolic flow in the UA or absent a-wave in the DV), then, delivery will be performed as soon as feasible. If fetal Doppler studies are borderline (brain sparing (MCA pulsatility index < 5th centile) or increased resistance in UA or DV (pulsatility index > 95th centile)), the Doppler will be repeated every 72 h, and delivery will be offered between 36 + 0 and 37 + 0 weeks.

Women assigned to the concealed/standard care pathway will have an sFlt-1/PlGF ratio taken, but the result will be concealed from the clinical team with their pregnancy being managed as per the local NHS guideline with delivery from 37 + 0 weeks.

In all cases, women will receive cCTG on the same day as ultrasound assessment and a minimum of twice weekly. If at any point cCTG demonstrates a short-term variability (STV) < 3.0 ms, then, delivery should be planned [62]. If at any point the attending clinical team feels the need to deviate from a care pathway, they will also be able to do so, with outcomes recorded on an intention-to-treat basis. Women who prefer not to be randomised into the PLANES study will be offered the opportunity to give blood for a sFlt-1/PlGF ratio test with the result being concealed and not used to guide clinical management.

### Outcome measures

This study will assess the feasibility of using a blood biomarker, sFlt-1/PlGF ratio, to safely refine the care pathway for the management of women with an SGA fetus from 32 weeks of pregnancy. Post hoc analysis of sFlt-1 and PlGF individually will also be conducted. The outcomes for the study have been separated into those that determine the feasibility of a definitive trial and those that address whether the intervention might have an effect on neonatal outcome or healthcare costs. Our group has had previous successful experience employing this approach in the ReMIT-2 study [63].

The feasibility outcomes are as follows: number of eligible women at each site, the number of women recruited, the number of women randomised, the number of women not compliant with the intervention and the reasons for this, reasons for not participating (patients may still consent to the perspectives work package who do not wish to participate in the main study) and number of women lost to follow-up. Women’s and birth partner’s views on the approach to recruitment, including consent, decision-making and length and content of trial information materials and views on the sFlt-1/PlGF test will also be gathered in the perspectives work package. Clinicians’ views on the acceptability of a future trial including potential barriers to recruitment, consent decisions, trial procedures and clinician training needs via questionnaires and a focus group or interview will be collected.

The proof of concept outcomes for mother includes the following: gestation and frequency of induction of labour or planned caesarean, frequency of maternal hypertensive disorders, intensive care admission or maternal death prior to discharge. The proof of concept outcomes for the baby include stillbirth, neonatal death, Apgar score at 5 min < 7, umbilical artery pH < 7.05, birthweight < 10th centile, admission to neonatal unit and length of stay, use of therapeutic cooling, length of stay in hospital and duration of respiratory support.

### Sample size and recruitment

As a feasibility study, success will be determined on the acceptability of the management approach for women and clinicians. Participants will be recruited directly from the fetal medicine, antenatal clinic or maternity assessment units at the nominated research sites. It is proposed that the study should expect to recruit in the region of 100 participants across two sites over a 12 month period. This is a pragmatic figure which is based on the typical number of SGA patients seen per annum in large consultant-led NHS units within the UK.

Participants will remain in the study for a maximum of 8 weeks (from 32 + 0 weeks [earliest point of eligibility] to estimated due date (EDD)). The study will end when the last recruited woman/baby is discharged from hospital after birth (up to age 1 month uncorrected) or the baby has reached their EDD.

### Enrolment and consent

Prior to taking part in the study, all women will have confirmation of their SGA status completed by their attending clinician based on an ultrasound scan performed within the preceding 72 h. Once a potential participant has been identified (all eligibility criteria met), they will be invited to take part in the study and a member of the clinical research team at site will discuss this with them. At this point, the woman and partner will receive written (PLANES patient information sheet (PIS)) and verbal information on the PLANES study, as well as an opportunity to ask questions and take any additional time required to consider taking part in the study. All potential participants will be given a unique screening ID that will subsequently be used to detail the reasons for the continuation or discontinuation at the screening stage. Participants willing to proceed will be asked to sign the study-specific informed consent form (ICF), and once written informed consent has been provided, participants will be registered onto the study and randomised by the research midwife/clinician at site.

The PLANES PIS will also include information regarding taking part in the perspective work package. If women are happy to take part in this, they will be asked to complete the relevant sections of the study ICF. Women who decline to take part in the main study will also be asked if they would like to take part in this perspective work package, and these participants will be expected to complete the standard participant ICF, initialling only those boxes relevant to the perspective study.

The research team are conscious that women may not feel that they should deviate from ‘normal’ NHS care despite the more detailed assessments of fetal wellbeing PLANES have set in place. In order to increase the ability of this study to inform a future RCT powered to prevent stillbirth, we will ask women who decline to be randomised whether they would consent to a single sFlt-1/PlGF ratio being taken and stored for processing only after the study has ended. In this way, we may still gain valuable information about the ability of this test to predict clinically relevant pregnancy outcomes even if women do not wish to be randomised.

The critical data in the PLANES study is derived from blood samples. Refusal to give the crucial blood sample at randomisation would result in significant compromise to the study. Therefore, any participant who does not provide this sample would need to be withdrawn from the study. Participants can refuse any further subsequent blood sample and remain in the study under the intention-to-treat principle.

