### Trial assessments and procedures

A prerequisite prior to randomisation of the participant into the PLANES study is a review of the participants medical and medication history; fetal assessments including computerised CTG and fetal ultrasound; and maternal observations including blood pressure, pulse and urinalysis. Once informed consent has been obtained, the participant will be asked to provide a blood sample for assessment of the sFlt-1/PlGF ratio. The participant will then be randomised to either the revealed or concealed pathway. At this time, the patient will also complete an EQ-5D-5L health questionnaire, and those consented to the perspectives work package will undertake a questionnaire and with additional patient consent either face-to-face or telephone interviews.

Continuing assessments will vary depending on the participant’s care pathway within the study; those in the control/concealed pathway receiving standard care and assessments on adverse events and standard care, outcomes will take place at the end of study. Participants within the revealed/biomarker led pathway will undergo blood pressure, pulse, urinalysis, computerised CTG and fetal ultrasound assessment as well as repeat sampling for sFlt-1/PlGF ratio as detailed below dependent on previous sFlt-1/PlGF ratio results and Doppler studies. In all cases, women will receive cCTG on the same day as ultrasound assessment and a minimum of twice weekly. Further assessments will take place after delivery and before discharge from hospital, and this will include a repeat EQ-5D-5L health questionnaire, childbirth experience questionnaire and recording of delivery outcomes, and following this in the postnatal period, assessments on maternal and neonatal outcomes will be completed (See Table 2).

**Table 2 Tab2:** Schedule of study-related assessments/procedures

Procedure		^a^Screening	^a^Baseline	Study visit 1	Study visit 2	Study visit 3	Delivery	Postnatal	End of study

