### Statistical analysis

Analysis of study data will take place once all participants have received the planned follow-up and all data is available. The likelihood of missing data is small given the standard procedure in place to manage the study centrally. Therefore, final analyses will take place on a complete-case basis with no adjustments made (e.g. multiple imputation) in the case of missing data.

A statistical analysis plan will be determined and finalised prior to final data lock. As the analyses being carried out are based on feasibility, the details in terms of the methodology may be altered during the course of the study. Patients will be summarised on an intention-to-treat basis retaining all patients irrespective of any protocol deviations. Further secondary analysis will be carried out on a per protocol population. Further analyses may be carried out on planned subgroups (e.g. those who meet the inclusion criteria for a future study) as is required. Multivariate data analysis techniques will be also used to attempt to find natural groupings in the generated data including hierarchical cluster analysis and principle component analysis. As this is an exploratory study, no formal levels of significance are set. All statistics presented will be presented alongside 95% confidence intervals so as to give an indication of the level of precision only. Continuous data will be summarised as median, interquartile range (IQR) and ranges, and categorical data shall be summarised as frequencies of counts and associated percentages. Quantitative analysis will involve simple descriptive statistics and the chi-square test for trend. Data from each method will be analysed separately then synthesised through the use of constant comparative analysis.

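### The mandatory first blood sample is placed both before and after randomisation; under the second order the withdrawal rule can remove women after open allocation, against the intention-to-treat statement

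*Protocol article*

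**What the plan says.** The protocol article describes the timing of the first sample in several places.

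- **Intervention:** "Following randomisation, women will be asked to provide a blood sample for assessment of sFlt-1/PlGF ratio". The sample comes after allocation.
- **Trial assessments and procedures:** "Once informed consent has been obtained, the participant will be asked to provide a blood sample for assessment of the sFlt-1/PlGF ratio", and then "The participant will then be randomised to either the revealed or concealed pathway". The sample comes before allocation.
- **Enrolment and consent**, on the enrolment sequence: "once written informed consent has been provided, participants will be registered onto the study and randomised by the research midwife/clinician at site". No sample is named as a condition.
- **Enrolment and consent**, on refusal: "Refusal to give the crucial blood sample at randomisation would result in significant compromise to the study". This does not say which step comes first. The rule that follows is that "any participant who does not provide this sample would need to be withdrawn from the study". Women who refuse a later sample, by contrast, stay in under the intention-to-treat principle.
- **Table 2** lists consent, randomisation and blood collection under one Baseline column, with no order within it.

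Two other statements matter. The Randomisation section says that participant, midwife and clinician cannot be blinded to the pathway. The Statistical analysis section says: "Patients will be summarised on an intention-to-treat basis retaining all patients irrespective of any protocol deviations". It adds that the final analyses use complete cases without imputation.

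**The concern.** A rule that withdraws women for lack of a sample is harmless before allocation. After an open allocation it is a post-randomisation exclusion. Because the article supports both orders, a site could follow either and believe itself compliant.

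Two things are at stake. First, under the Intervention order the withdrawal rule and the promise to retain all patients cannot both be honoured if a withdrawn woman also leaves the analysis. Second, Outcome measures lists the numbers recruited, randomised, non-compliant and lost to follow-up as feasibility outcomes. The same refusal would be counted differently under the two orders, and these counts are meant to inform the design of the definitive trial.

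**Working it through.** **Step 1. Follow one woman who consents but gives no first sample.**

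| | Order in Intervention | Order in Trial assessments and procedures |
|---|---|---|
| Sequence | consent, randomise, request sample | consent, request sample, randomise |
| Knows her pathway when she refuses? | yes | no |
| Effect of the withdrawal rule | removed after allocation | stopped before allocation |
| Counted as randomised? | yes | no |
| Counted as a loss after randomisation? | yes | no |
| Conflict with retaining all patients? | yes, if withdrawal also means leaving the analysis | none |

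**Step 2. Does any other section settle the order?** No. Enrolment and consent passes from consent to randomisation without mentioning a sample, its refusal rule ties the sample to randomisation without ordering the two, and Table 2 groups all three steps.

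**Step 3. Does withdrawal mean leaving the analysis?** The article does not say so outright. Enrolment and consent does set these women against those who refuse later samples and stay in under intention-to-treat, so it leans that way. In addition, under the complete-case rule a withdrawn woman with no outcomes collected would drop out of the summaries.

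**Step 4. Size of one withdrawal.** The inputs are about 100 women (Sample size and recruitment) and a 3:1 ratio (Randomisation).

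- Revealed: 100 × 3/4 = 75. Concealed: 100 × 1/4 = 25.
- One withdrawal: 1/75 = 1.3% of the revealed arm; 1/25 = 4.0% of the concealed arm.

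**Step 5. Illustration over assumed refusal rates.** The article states no refusal rate. The rates r below are assumptions and are set equal in both arms. Expected losses after randomisation are 75r and 25r. The chance of at least one concealed-arm loss is 1 − (1 − r)^25.

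| Assumed r | Expected revealed losses | Expected concealed losses | Chance of at least one concealed loss |
|---|---|---|---|
| 2% | 1.5 | 0.5 | 40% |
| 5% | 3.75 | 1.25 | 72% |
| 10% | 7.5 | 2.5 | 93% |

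If the sample always precedes randomisation, the rule causes no loss after randomisation at any r.

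**Step 6. Effect on the feasibility counts.** Take 100 consenting women and r = 5% (assumed). Under the Intervention order, 100 are randomised and 5 are then withdrawn. Under the other order, 100 − 5 = 95 are randomised and none is withdrawn by this rule. The women behave identically, but the randomised and retained figures differ.

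The article states no figure that depends on this point, so there is nothing of its own to reproduce.

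**The case against.** The best defence is that Trial assessments and procedures is the step-by-step account and that sites would follow it. Under that order there is no breach. A reader might infer that the article flatly contradicts its intention-to-treat statement. It does not: the conflict needs both the Intervention order and a reading of withdrawal as removal from the analysis. That part of the defence stands. The two orders still coexist, and nothing ranks one above the other.

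Three further inferences are tempting but not supported.

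- **Losses will be heavier in the concealed arm.** A concealed result does not guide that woman's care, so refusal could depend on arm. But no refusal rate is given, and these women have just consented to a study built on this test. The article also plans to ask women who decline randomisation for a concealed sample, which tells against lack of personal benefit as a strong driver of refusal.
- **The baseline EQ-5D-5L is contaminated by allocation.** The text reads "The participant will then be randomised to either the revealed or concealed pathway. At this time, the patient will also complete an EQ-5D-5L" questionnaire. This can mean the same contact rather than a moment after disclosure. The economic aim is the feasibility of data collection, and no baseline-adjusted comparison is stated. The wording merits clarification only.
- **The randomised comparison is broken.** No formal significance levels are set, intervals are for precision only, and success rests on acceptability.

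It can also be said that separate counts of recruited, randomised and lost women would make a refusal visible. That is true at any one site. It does not help if the sites follow different orders and their counts are pooled.

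**Conclusion.** The point holds as an internal inconsistency with a conditional consequence. The article gives two incompatible orders for a mandatory sample and attaches a withdrawal rule to it. Under one order the rule can remove women after open allocation and conflicts with retaining all patients; under the other it does not. In either case, the meaning of the randomised, non-compliant and lost-to-follow-up counts is not fixed until one order is chosen.

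Each withdrawal is worth 4% of the concealed arm or 1.3% of the revealed arm, assuming about 100 women split exactly 75:25. The total number affected cannot be stated, because no refusal rate is given, and a difference between arms is a possibility only. Severity is moderate: it should be settled because the affected counts are the study's own outcomes, but no hypothesis test depends on it.

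**What to change.** 1. State one order in Intervention, Enrolment and consent, and Trial assessments and procedures: consent, blood sample, then randomisation.
2. Make the sample a condition of randomisation. A woman who refuses it is counted as consented but not randomised.
3. For randomised women, replace the withdrawal rule with retention in the intention-to-treat set. Report missing or unanalysable first samples by arm.
4. As a minor clarification, state that the baseline EQ-5D-5L is completed before the allocation is disclosed.

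The cost is protocol wording and site instructions. Table 2 already places consent, sample, questionnaire and randomisation under Baseline. Its first footnote suggests that these steps may not always fall at one contact, so the instructions should say that the sample is drawn before the randomisation system is accessed.
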